## Abstract

**Background:**

Cognitive decline and dementia represent a key problem for public health as they heavily impair social functioning and independent living. The development of new strategies to support recommendations for patients and their caregivers may represent an outstanding step forward.

**Aims:**

To describe the study protocol and methods of “My Mind Project: the effect of cognitive training for elderly” (Grant No. 154/GR-2009-1584108), which investigates, by the use of a multidisciplinary approach, the effects of a comprehensive cognitive training programme on performances in aged subjects with mild–moderate Alzheimer’s disease, mild cognitive impairment and normal cognitive functioning.

**Methods:**

The study is a prospective randomized intervention for the assessment of cognitive training effects in three groups of elderly subjects with different cognitive status. A total of 321 elderly people were enrolled in Marche Region, Italy. Each subject was randomly assigned to an experimental group or to a control group. Cognitive performances and biochemical blood markers have also been analysed before cognitive training (baseline), immediately after termination (follow-up 1), after 6 months (follow-up 2) and after 2 years (follow-up 3).

**Discussion:**

The results will be useful to identify some efficient programmes for the enhancement of cognitive performance in elderly with and without cognitive decline.

**Conclusion:**

The application of a non-pharmacological approach in the treatment of elderly with cognitive disorders could have a profound impact on National Health Service.

## Introduction

Cognitive decline and dementia are pathological conditions that may heavily affect social functioning and independent living. Elderly are particularly susceptible to cognitive diseases, particularly mild cognitive impairment (MCI). Previous studies have evidenced that the annual conversion rates from MCI to Alzheimer’s disease (AD) vary from 5 to 20 % [1], with higher rates in subjects with subjective memory complaints.

To reduce the incidence of these diseases, it is pivotal to identify the treatments that prevent or delay the cognitive decline as well as its progression to dementia. Pharmacological therapies currently available have been proved to be no effective [2], but positive results have been shown by the use of cognitive training, in particular to enhance or regain specific functions, such as memory and attention processes, with a positive impact on subjective well-being, mood status and quality of life of elderly people [3].

The identification of the processes involved in cognitive decline is another key issue, and a multidisciplinary approach might be particularly suitable.

The “My Mind Project” aimed to analyse several aspects related to cognitive performances before and after a cognitive and comprehensive intervention as well as the possible changes in potentially related peripheral biomarkers. Indeed, the variations in cognitive status can be reflected by the modulation of systemic biological parameters. We decided to focalize the attention on the following biomarkers: brain-derived neurotrophic factor (BDNF, lymphocytes mRNA and plasmatic protein), platelet total phospholipase A_2_ (tPLA_2_) activity, the ratio between the levels of two platelet amyloid precursor protein (APP) forms, trace elements, monocyte expression profiling as well as oxidative stress evaluation.

BDNF, a neurotrophin associated with activity-dependent synaptic modulation, is widely expressed in brain structures involved in learning and memory and is also produced by immunocompetent cells [4]. Many studies have taken into account the peripheral blood BDNF levels in AD patients, but data are controversial. Discrepancies are difficult to explain as they might be due to heterogeneity in disease staging [5], not the evaluation of drug use and depressive symptoms [6], underestimation of smoking and alcohol intake impact [7].

PLA_2_ comprises a superfamily of enzymes involved in a wide variety of physiological processes, including phospholipid metabolism, remodelling of cell membranes and intracellular signalling. Cerebral PLA_2_ influences the non-amyloidogenic processing of APP [8], and its functional alterations may have consequences on amyloid-beta peptides (Aβ) production. The use of platelet tPLA_2_ as peripheral biomarker of the neuronal enzyme is peculiarly convincing in the light of the recent finding that *total* PLA_2_ activity in the thrombocytes may specifically mirror the *total* activity in the brain [9].

Aβ, present in the extracellular plaques of AD brain tissue [10], originates by proteolytic processing of APP, a transmembrane protein abundantly expressed in the brain and the peripheral tissues such as platelets. It has been reported that AD platelets show a reduced ratio between the levels of two APP forms, observed as two immunoreactive bands at 130 and 106–110 kDa in Western blotting assays. The APP form ratio allows to detect AD at an early stage and to differentiate it from other types of dementia [11].

Another important aspect regards the role of the immune system in AD pathogenesis. Several evidences support the idea of a brain–immune system breakdown as a potential pathological mechanism in AD [12]. In AD, mononuclear phagocytes (MP) are inefficient [13], and the accumulation of the metabolic end-product Aβ might be due to the failure of the innate immune system. The molecular mechanisms and the gene pathways involved in monocytes deregulation are unknown. Taking into account that also trace elements are essential for optimal immune system function [14], it is increasingly important to understand the process that governs this response in AD. In recent years, it has become evident that trace elements, particularly zinc (Zn), copper (Cu), iron (Fe) and selenium (Se), may play a role in the pathogenesis of AD [15]. Conversely, the possible relationship existing among plasma trace elements levels and performance on cognitive function tests is not well known.

The biological activity of some antioxidant enzymes (superoxide dismutase, glutathione peroxidase, catalase) also contributes to the immune response. In this context, it seems that oxidative stress is mechanistically and chronologically associated with lifestyle-related risk factors for AD and cognitive decline [16]. Indeed, several studies have shown that there is a relationship between lifestyle, healthy dietary patterns and reduced risk of dementia and cognitive decline, as highlighted by all six cross-sectional studies and six of eight longitudinal studies examined in the systematic review of Van de Rest et al. [17]. Physical activity, even moderate, and participation in recreational activities may have a protective effect on mental function and incidence of dementia [18].

The innovative contribution of the My Mind Project (Grant No. 154/GR-2009-1584108 founded by the Italian Ministry of Health and the Marche Region) consists in identifying a comprehensive intervention (training and parameters, both cognitive and biological, useful in monitoring its efficacy) with the scope to develop a multidisciplinary approach to cognitive disease in elderly people. In particular, the use of multidimensional assessment includes the analysis of interrelationships between cognitive, psycho-social and biochemical aspects.

## Methods/design

### Study design

It is a prospective randomized intervention study for the assessment of the effects of cognitive training in three groups of elderly subjects with different cognitive status, using a multidisciplinary approach. The project has a duration of 4 years. Three follow-up phases have been carried out, as shown in Fig. 1

**Fig. 1 Fig1:**
[figure not shown]
Flow chart of the study

### Recruitment and screening phase

Subjects were enrolled from the Evaluation of Alzheimer’s unit of Geriatrics Operative Unit at the INRCA Hospital in Fermo (Italy) (Fig. 1). The project started on 1 June 2012 and will last until 11 June 2016. Patients were diagnosed with AD or MCI by means of an extended neuropsychological and functional evaluation, neuroimaging and laboratory tests, according to diagnostic guidelines. Healthy elderly (HE) consisted of age-matched individuals who underwent the same clinic and neuropsychological assessment as the other groups. The status of HE was defined as the absence of relevant cognitive diseases.

### Sample

Three hundred and twenty-one community-dwelling elderly subjects (aged ≥65 years) living in Marche Region were enrolled and divided into three groups, according to their cognitive status: 111 subjects without relevant cognitive diseases (HE), 109 subjects with MCI and 101 subjects affected by mild–moderate AD.

### Inclusion and exclusion criteria

Eligibility has been determined after a complete medical and neuropsychological examination to assess the inclusion/exclusion criteria.

The inclusion criteria included (a) subjects aged 65 years or older, (b) availability during the training and testing phases, (c) presence of a caregiver for subjects with cognitive decline (AD and MCI subjects).

Exclusion criteria included (a) the presence of serious medical and psychiatric conditions, and sensori-motor deficits that would prevent the participation in the training; (b) participation in previous cognitive training; (c) subjects with severe AD; (d) the presence of neurodegenerative disorders different from AD.

### Randomization

After the enrolment, the subjects have been assigned to the experimental group (EG) or the control group (CG) and performed a first evaluation, as shown in Fig. 1.

### Sample size calculation

It was based on the null hypothesis that proportion of “success” and “failure” to the intervention is equal in the two groups of subjects (i.e. EG and CG), such as OR = 1.

Success and failure were defined differently for each group of subjects (i.e. HE, MCI, AD) on the basis of a significant variation in the primary outcomes (see below).

Considering an OR = 1.5 indicative of an effect of cognitive training, a total sample of 300 subjects (i.e. 100 subjects per group) allow to reach a 90 % of statistical power using logistic regression at the 5 % level (two-tailed). Drop-out rate was set at 20 %; indeed, a total of 321 subjects were recruited.

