### Statistical analysis

Analysis will be carried out by the software SPSS 16 (SPSS Inc. Chicago, Illinois), separately for each group of subjects and across groups.

Descriptive analysis will be used to check the distribution of the data. Bivariate analysis will be used to compare within each group the characteristics of experimental and control groups, by chi-square for frequencies and *t* test for continuous variables. Paired tests will be used to check for the variation in cognitive measures before and after intervention within each group. General linear models will be used to verify the effect of intervention in the outcome measures, adjusting for covariates.

Each subject will be classified on the basis of primary outcomes and then included in multiple logistic regression models to identify the predictors of improvements in cognitive status, adjusting for covariates. Repeated-measures ANOVA will be used to examine the training effect on biochemical parameters adjusted for age and sex. The significance level will be set at *P* < 0.05.

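### The stated 90% power for OR = 1.5 with 300 subjects cannot be right: power is at most about 42% pooled and about 17% within each cognitive group

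*Protocol article*

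**What the plan says.** All of the power statement is in the Sample size calculation section of the protocol article.

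- Null hypothesis: "proportion of “success” and “failure” to the intervention is equal in the two groups of subjects (i.e. EG and CG), such as OR = 1".
- Effect: "Considering an OR = 1.5 indicative of an effect of cognitive training".
- Power claimed, method and test level: "90 % of statistical power using logistic regression at the 5 % level (two-tailed").
- Number of subjects said to give that power: "a total sample of 300 subjects (i.e. 100 subjects per group) allow to reach a".
- Endpoint: "Success and failure were defined differently for each group of subjects (i.e. HE, MCI, AD"). The primary outcome section gives the three definitions: a fall of at least two points on ADAS in AD, a gain of 1.5 words on the List of Words in healthy elderly (HE), and a gain of 0.5 on the Word Pairs Learning Test in MCI.

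The Statistical analysis section runs the analysis "separately for each group of subjects and across groups". The Sample section reports enrolment of "111 subjects without relevant cognitive diseases (HE), 109 subjects with MCI and 101 subjects affected by mild–moderate AD".

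The article gives neither the control success rate nor the EG:CG allocation ratio.

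**The concern.** An odds ratio of 1.5 is a modest difference between two proportions: 45% v 55% at mid-range. Comparing two arms of 150 on a binary endpoint would not normally give 90% power for it, and two arms of 50 fall much further short.

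The figure is the trial's only justification for its size. If it is wrong, the logistic regression on the success outcome is far more likely than not to miss an effect that the plan itself regards as showing that training works. A reader told that power was 90% would have good reason to take a non-significant odds ratio as evidence against training.

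**Working it through.** **Inputs from the article.** Binary success or failure, EG v CG, null OR = 1, alternative OR = 1.5, two-sided 5%, N = 300 in total or 100 per cognitive group, stated power 90%.

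**Inputs not given.** The control success rate p1 was scanned from 0.02 to 0.975. Allocation was taken as 1:1, the choice most favourable to power.

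**Formulas.** With n per arm:

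- EG rate: p2 = 1.5·p1 / (1 − p1 + 1.5·p1).
- Null standard error: SE0 = √(2·p̄(1 − p̄)/n), with p̄ = (p1 + p2)/2.
- Alternative standard error: SE1 = √([p1(1 − p1) + p2(1 − p2)]/n).
- Power = Φ((p2 − p1 − 1.96·SE0)/SE1).

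In large samples this two-proportion test is equivalent to logistic regression on the arm indicator alone.

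**Attempt to reproduce 90% at the most favourable control rate, p1 = 0.45.**

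- p2 = 0.675/1.225 = 0.551, so the difference is 0.1010.
- 150 v 150: SE0 = 0.0577, SE1 = 0.0574. Power = Φ((0.1010 − 0.1132)/0.0574) = Φ(−0.21) = 41.6%.
- 50 v 50: SE0 = 0.1000, SE1 = 0.0995. Power = Φ((0.1010 − 0.1960)/0.0995) = Φ(−0.95) = 17.0%.
- Subjects per arm for 90% power: (1.96·√(2p̄(1 − p̄)) + 1.2816·√(p1(1 − p1) + p2(1 − p2)))² / 0.1010² = 512.7, so 513 per arm or 1,026 in total.

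**Across control rates, OR = 1.5.**

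| CG success | EG success | Power, N = 300 | Power, N = 100 | n per arm for 90% |
|---|---|---|---|---|
| 10% | 14.3% | 20.5% | 9.6% | 1,219 |
| 20% | 27.3% | 31.6% | 13.4% | 716 |
| 30% | 39.1% | 38.3% | 15.8% | 569 |
| 40% | 50.0% | 41.3% | 16.9% | 519 |
| 45% | 55.1% | 41.6% | 17.0% | 513 |
| 50% | 60.0% | 41.3% | 16.9% | 519 |

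**Cross-checks on the maxima.** A Wald test on the log odds ratio gives 41.6% and 17.1%. Exact binomial power of the chi-square test gives 43.9% and 18.8%.

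**Other readings, maximum power over all control rates.**

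| Reading | Maximum power |
|---|---|
| One-sided 5%, N = 300 | 54.2% |
| All 321 enrolled | 44.0% |
| 2:1 allocation, N = 300 | 37.9% |
| 100 per arm | 29.7% |
| 300 per arm | 69.8% |
| 300 per arm, one-sided | 79.8% |
| Enrolled HE / MCI / AD (111 / 109 / 101) | 18.4% / 18.1% / 17.1% |

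None reaches 90%.

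**Odds ratio detectable at 90% power, control success 20% to 50%.**

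| Arms | Pooled two-proportion test | Wald logistic test |
|---|---|---|
| 150 v 150 | 2.12 to 2.33 | 2.14 to 2.36 |
| 50 v 50 | 3.73 to 4.07 | 3.95 to 4.48 |

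At 30% control success with 50 v 50, the Wald test needs OR 3.97 (30% v 63%) and the pooled test OR 3.75. At 10% control success the pooled test needs 2.84 (150 v 150) and 5.27 (50 v 50).

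**A possible source of the figure (inference only).** The logistic formula for a continuous covariate, with the odds ratio expressed per standard deviation, is N = (1.96 + 1.2816)² / (P(1 − P)·(ln 1.5)²). With P = 0.308 this is 10.507/(0.308 × 0.692 × 0.1644) = 300. A 1:1 arm indicator has variance 0.25 instead of 1, so it needs about four times as many, about 1,199. The article does not say that this formula was used, and the result above does not depend on it.

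**The case against.** - **The missing inputs might rescue the claim.** A journal article condenses its protocol, and the full document may give a control rate and an allocation ratio. This fails: the control rate was scanned over nearly its whole range, and unequal allocation lowers power.
- **The 90% may refer only to the pooled 300.** This is the natural reading, since the power is attached to the total, and the article does not expressly claim 90% within each group. The pooled figure should therefore lead. The per-group figure still matters, because success is a different endpoint in each group and separate analyses are planned.
- **The ceilings are approximate.** This stands. 42% and 17% come from a normal approximation; exact power is about two points higher.
- **A single detectable odds ratio would also mislead.** This stands. It depends on the control rate and somewhat on the test, so it should be given as a range or with its assumption.
- **Other analyses may have more power.** General linear models on the scores and covariate adjustment are planned, and their power was not calculated. The conclusion is therefore confined to the binary success outcome. That is the outcome the power statement is about, and the statement claims no gain from adjustment.
- **Enrolment is complete, so conduct cannot change.** This is true, and it is why the correction is to wording and interpretation.

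**Conclusion.** The stated 90% power is wrong. For EG v CG at OR = 1.5, two-sided 5%, power with 300 subjects is about 20% to 42% for control success of 10% to 60%. Within a group of 100 it is about 10% to 17%. At the best case the binary analysis would miss the stated effect about 58% of the time pooled (100 − 42) and about 83% of the time per group (100 − 17). Reaching 90% needs at least about 1,026 subjects for a single comparison, more than three times the 300 stated (1,026/300 = 3.4).

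This rests on 1:1 allocation, an unadjusted comparison of the arms, and normal approximations. The exact calculation and the alternative readings leave the conclusion unchanged. The error must be corrected because the trial's justification depends on it.

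**What to change.** Keep the sample and replace the power sentence in the Sample size calculation section. The new text should:

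1. State the assumed control success rate and allocation ratio, for each cognitive group where they differ.
2. State that power for OR = 1.5 is at most about 42% with 300 pooled and about 17% with 100 in one group, as approximate maxima under 1:1 allocation.
3. State the odds ratio detectable at 90% power with its assumption: about 2.2 pooled (2.1 to 2.4 for control success of 20% to 50%) and about 4 per group (3.7 to 4.5 over the same range, depending on the test).
4. Add that a non-significant odds ratio is not evidence that training has no effect, and that odds ratios will be reported with confidence intervals.

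The cost is wording only, with no extra subjects and no change to conduct. The stated power becomes much less favourable.

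### Recruiting 321 does not provide the stated 20% drop-out allowance on 300: about 257 would remain, and all three groups would fall below 100

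*Protocol article*

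**What the plan says.** The Sample size calculation section of the protocol article states that "a total sample of 300 subjects (i.e. 100 subjects per group) allow to reach a 90 % of statistical power", for a two-sided 5% test by logistic regression. The effect is given as follows: "Considering an OR = 1.5 indicative of an effect of cognitive training". The comparison is between the experimental group (EG) and the control group (CG), with a null hypothesis that the proportion of successes "is equal in the two groups of subjects (i.e. EG and CG), such as OR = 1".

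The next sentence deals with losses: "Drop-out rate was set at 20" per cent, followed directly by "indeed, a total of 321 subjects were recruited".

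The Sample section breaks the 321 down as "111 subjects without relevant cognitive diseases (HE), 109 subjects with MCI and 101 subjects affected by mild–moderate AD".

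Nothing in the article says that the 300 already contains an allowance for drop-out, or that the 20% applies to some other base.

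**The concern.** As the two sentences are joined, the reader is told that 300 evaluable subjects are needed, that 20% may be lost, and that 321 were therefore recruited. But 321 exceeds 300 by only 21 subjects, which is far too few to absorb a 20% loss. The margin is also uneven: the AD group has one subject to spare.

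The group sizes matter because the Statistical analysis section plans analyses within each diagnostic group as well as across groups, and the primary outcome is a different measure in each group. Follow-up runs to 2 years in an elderly population, part of it with dementia, so the allowance is likely to be needed. A reader who takes the section at face value would believe that the required 300, and the power attached to it, survive a 20% loss. On the plan's own figures they do not.

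**Working it through.** **Inputs**

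- From Sample size calculation: required N = 300 (100 per group); drop-out d = 20%; recruited 321; OR = 1.5; power 90%; two-sided 5%.
- From Sample: HE 111, MCI 109, AD 101. The sum is 111 + 109 + 101 = 321, so the two sections agree on the total.
- Not given in the article: the control success rate and the allocation ratio. They are needed only in step 5, where they are assumed.

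**1. Can 321 be reproduced from 300 and 20%?**

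- Standard inflation, N/(1 − d): 300/0.8 = 375, or 100/0.8 = 125 per group.
- Common shortcut, N × (1 + d): 300 × 1.2 = 360, or 120 per group.

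Neither gives 321, which is 54 below 375 and 39 below 360.

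**2. What remains of 321 after a 20% loss?**

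| | Recruited | × 0.8 | Required | Short by about |
|---|---|---|---|---|
| Total | 321 | 256.8 | 300 | 43 |
| HE | 111 | 88.8 | 100 | 11 |
| MCI | 109 | 87.2 | 100 | 13 |
| AD | 101 | 80.8 | 100 | 19 |

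**3. What loss does the recruited number cover?** The formula is 1 − required/recruited.

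- Total: 1 − 300/321 = 6.5%
- HE: 1 − 100/111 = 9.9%
- MCI: 1 − 100/109 = 8.3%
- AD: 1 − 100/101 = 1.0%

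**4. Effect on power if the plan's 90% at 300 is accepted.** The standardised effect that gives 90% power at two-sided 5% is 1.96 + 1.28 = 3.24. It scales with the square root of the sample size: 3.24 × √(257/300) = 3.00. Power is then Φ(3.00 − 1.96) = Φ(1.04), about 85%. On the plan's own terms the drop-out error alone costs about 5 percentage points.

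**5. Power computed directly for the two-arm comparison.** Assumptions: 1:1 allocation, OR = 1.5, two-sided 5%, control success rates from 0.10 to 0.60, normal approximation for two proportions.

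| Control rate | EG rate at OR 1.5 | Power, N = 300 | Power, N = 257 |
|---|---|---|---|
| 0.10 | 0.143 | 20.5% | 18.1% |
| 0.30 | 0.391 | 38.3% | 33.6% |
| 0.45 | 0.551 | 41.6% | 36.6% |
| 0.60 | 0.692 | 38.6% | 33.9% |

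The best case is at a control rate of about 0.45: about 42% with 300 and about 37% with 257. Within a single group of 81 to 89 completers, power is about 9% to 16%, and the best cases are 14.5% to 15.6%. Most of the gap to 90% therefore comes from the base figure of 300, not from drop-out. In this calculation too, drop-out removes at most about 5 points.

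**The case against.** Five points can be made for the plan.

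- **321 is a count of people recruited, not a calculated target.** The plan may have aimed higher and fallen short, so that the link to 20% is only loose drafting. No higher target is stated, however, and the sentence offers 321 as what follows from the 20%. If recruitment did fall short, the section should say so.
- **The 20% may describe loss by the 2-year visit.** The training lasts about 2 months and the primary outcome is assessed after it, so fewer subjects might be missing at that point. The section does not say when the 20% applies. This point stands in part: the shortfall in the primary analysis could be smaller than 43. Even so, any loss above 6.5% overall, or above 1.0% in AD, takes the numbers below the stated requirement.
- **The figure in error may be 300, not the allowance.** The usual logistic regression formula for a continuous covariate (OR 1.5 per standard deviation, success rate 0.5, 90% power) gives 256, and 256/0.8 = 320, close to 321. The text does not say this. It names 300, and its comparison is between two arms, which is a binary predictor. If this was the source, the section still needs correcting.
- **The 90% is attached to the total.** On that reading, 100 per group only describes how the total is made up, and a group below 100 breaks no separate power statement. That is fair as to the power claim. The group sizes are nevertheless stated as required, and analyses within groups are planned.
- **Some margin exists.** This is true: 321/300 is 7% more than required. What is missing is the 20% allowance, not all allowance.

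**Conclusion.** The concern holds: the allowance is wrong as written. No standard calculation turns 300 and 20% into 321, and no other section of the article repairs it. At 20% drop-out about 257 subjects are expected, 43 short (14% of 300), with about 89 HE, 87 MCI and 81 AD. These figures rest only on numbers printed in the article and on the 20% applying equally to each group.

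The cost in power attributable to this error is modest: from 90% to about 85% if the plan's base is accepted, and at most about 5 points when power is computed directly. The much lower absolute values in that direct calculation (at best about 37% pooled and about 15% within a group) rest on the assumed 1:1 allocation and range of control rates. They come mainly from the separate fault in the base of 300. Raising recruitment to 375 would not have brought the trial to 90%.

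**What to change.** Restate the drop-out sentence in Sample size calculation in one of two ways:

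1. say that the 321 recruited allow for a 6.5% loss overall (HE 9.9%, MCI 8.3%, AD 1.0%); or
2. keep the 20% and say that about 257 completers are expected (89 HE, 87 MCI, 81 AD), fewer than the 300 stated as required.

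In either case, name the visit to which the drop-out rate refers. Give the power or the expected confidence interval width for the expected completers, in total and within each group, together with the control success rate and allocation ratio used. Do not describe 321 as including a 20% allowance. If the requirement was in fact a figure other than 300, state that figure and how it was obtained.

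The cost is wording and a short recalculation. No further subjects are needed and the conduct of the trial does not change, but the stated position becomes less favourable. The correction is best made together with that of the base calculation, because correcting the allowance alone would leave an unsupported 90% in place.
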